#### Safety outcome variables

Adverse event: The investigator will check for adverse drug reactions during hospital rounds and educate patients to report any adverse events. Information includes the date of occurrence and disappearance, severity, treatment, and other suspected drugs.Vital sign: For each visit, blood pressure and heart rate will be recorded.Laboratory tests: Complete blood count (hemoglobin, hematocrit, white blood cell, and platelet count) and blood chemistry (glucose, blood urea nitrogen, creatinine, estimated glomerular filtration rate, total protein, albumin, bilirubin, aspartate aminotransferase, alanine aminotransferase, alkaline phosphatase, γ-gamma glutamyl transpeptidase (visit 1), sodium, potassium, chloride, total cholesterol, low-density lipoprotein, high-density lipoprotein, triglycerides, lipoprotein (a), and hemoglobin A1c (visit 1)).Concomitant drugs: All drugs taken 4 weeks before the screening visit will be recorded. After each visit, name, daily dose, route, duration, and reason for administration for each drug were recorded in the electronic case report form (eCRF).Clinical results: Data on all clinical outcomes (death, recurrent myocardial infarction, heart failure, stroke, new-onset atrial fibrillation, and prolonged hospitalization) will be collected and relevant source documents will be submitted. Prolonged hospitalization has been defined as a hospital stay of more than 10 days. If the patient is admitted to another hospital, the investigator will try to collect as much data as possible. Follow-up will be continued for 1 month during outpatient visits, or through phone calls.

### Plans to promote participant retention and complete follow-up {18b}

Patients will be fully informed about the trial objectives and safety issues. Patients are allowed to drop out at any time during the trial; however, completion will be encouraged. Follow-up will be continued for 30 days after surgery and will emphasize the importance of routine postoperative checkups regardless of the study, especially during outpatient follow-up.

### Data management {19}

Information will be entered into the electronic case report form (eCRF), and access is given only to relevant medical staff within the hospital. Data collected from each subject during the investigation were accurate and complete on the eCRF. Electronic medical records will be stored for at least 3 years after trial termination and publication of the final report. Details of record preservation follow local regulations.

### Confidentiality {27}

All records of trial subjects remain confidential, not disclosed to the public, and protected by law of confidentiality. They will be registered based on identification number and initials in the eCRF, and their names will not be recorded. If the subject’s name is recorded in any other document, it must be deleted before a copy is taken. All records of the clinical trial, including those saved on a computer, should be kept safe, in accordance with the national data protection law.

In addition, subjects are fully informed that all personal information is handled in a strictly confidential manner, in accordance with the Data Protection Law, even when trial results are published or reported.

### Plans for collection, laboratory evaluation, and storage of biological specimens for genetic or molecular analysis in trial/future use {33}

There are no biological specimens to be collected nor stored.

## Statistical methods

### Statistical methods for primary and secondary outcomes {20a}

Statistical methods for this clinical trial will be two-tailed tests with a significance level of 0.05. Continuous variables will be presented as descriptive statistics (average, standard deviation, median, minimum, and maximum). Categorical variables will be presented as descriptive statistics (frequency and percentage).

#### Primary efficacy evaluation

The maximum change in troponin-I between peak and baseline during the first 3 days will be presented as descriptive statistics and tested with an independent t-test or Wilcoxon’s rank-sum test.

#### Secondary efficacy evaluation

AUC (area under the ROC curve) of both troponin-I and CK-MB for 3 days and maximum change of CK-MB over 3 days compared to baseline level after evolocumab administration will be tested with independent t-test and Wilcoxon’s rank sum test. Changes in troponin-I levels at each visit compared to the initial level will be analyzed with repeated ANOVA.

Changes in CK-MB, brain natriuretic peptide (BNP), and CRP level compared to baseline levels will be analyzed with repeated ANOVA.

Changes in left ventricular ejection fraction at 3 days from baseline will be analyzed with an independent t-test and Wilcoxon’s rank-sum test. For comparison within the group, a paired t-test or Wilcoxon’s signed rank test will be used.

Cumulative mortality, recurrence rate of myocardial infarction, incidence of stroke, new atrial fibrillation, and incidence of coronary revascularization 1 month after the procedure will be analyzed using the Kaplan-Meier method. Differences between the two groups will be tested using the log-rank test. In this analysis, no missing values will be used.

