### Sample size {14}

The objective of this trial is to evaluate whether evolocumab effectively prevents post-CABG myocardial injury in patients with multivessel CAD. The peak Troponin-I level during the first three postoperative days compared to the initial level was evaluated as the primary outcome. Based on studies by Kaushik et al. on the efficacy of statin in preventing myocardial injury in CABG patients, the difference between peak Troponin-I versus initial level was 1.00±1.34 ng/mL in the statin loaded group and 2.25±2.59 ng/mL in the control group [6]. Therefore, with the power of 0.8 and significance level of 0.05, the change of Troponin-I at the time of peak compared to the base point can be calculated as 1.00±1.34ng/mL in the evolocumab group and 2.25±2.59ng/mL in the control group. According to the Power Analysis & Sample Size (PASS) 16 program, a minimum of 45 people per group are required for validation and a potential dropout rate of 10%, 50 people per group, and a total of 100 people are required for this clinical trial.

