## Assignment of interventions: allocation

### Sequence generation {16a}

Subjects who agree to participate in this trial will sequentially receive subject identification codes in the order of their screening visit. Patients are randomly assigned to ensure scientific validity, maximize comparability between groups, and avoid bias. Those who meet the eligibility criteria will be divided into two groups, with the stratified block randomization method used due to multi-institutional sampling. An independent statistician will produce random allocation numbers using the Statistical Analysis System (SAS) ver. 9.4, Microsoft Windows (SAS Institute Inc., Cary, NC, USA), which will then be distributed to the subjects.

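### Four secondary outcomes get a t-test and a rank-sum test with no rule on which decides, LVEF is compared by unadjusted change score with no hospital term, and the within-group tests are not labelled descriptive

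*Protocol article*

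**What the plan says.** All of this is in the protocol article.

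- **Enzymes (Secondary efficacy evaluation, under Statistical methods).** The troponin-I AUC, the CK-MB AUC and the maximum CK-MB change "after evolocumab administration will be tested with independent t-test and Wilcoxon"'s rank-sum test. The two tests are joined by *and*. CK-MB change by visit is separate and gets repeated ANOVA only.
- **LVEF (same section).** "Changes in left ventricular ejection fraction at 3 days from baseline will be analyzed with an independent t-test", again together with a rank-sum test.
- **Within-group tests (same section).** Directly after the LVEF sentence: "For comparison within the group, a paired t-test", or a signed rank test. Nothing marks these as descriptive.
- **Primary outcome, for contrast (Primary efficacy evaluation).** The same two tests are joined by *or*.
- **Level (Statistical methods, item 20a).** "two-tailed tests with a significance level of 0.05".
- **Randomisation (Sequence generation, item 16a).** "stratified block randomization method used due to multi-institutional sampling". None of the named analyses is described with hospital as a factor, and item 20b states that no additional analyses are planned.
- **Data available (Table 1).** Transthoracic echocardiography is scheduled at V1 and V6, so baseline LVEF is already collected.

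**The concern.** A t-test compares means and a rank-sum test compares rank ordering. On skewed data they can disagree, and the text does not say which result stands when they do. The trial is open to investigators, so a choice made after the data are seen could be made with the arms known.

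The within-group tests ask whether each arm changed from its own baseline. LVEF may shift after surgery in both arms whatever the drug does. A significant paired test in one arm beside a non-significant one in the other is easily read as a drug effect, but it is not a comparison of the arms.

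The third issue is precision. With 45 evaluable patients per arm, a change-score comparison without baseline as covariate, and without the factor used to stratify randomisation, gives up information the trial has already collected.

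**Working it through.** **1. The plan's own figure.** Inputs from Sample size (item 14): "1.00±1.34ng/mL in the evolocumab group and 2.25±2.59ng/mL in the control group", "with the power of 0.8 and significance level of 0.05". The root-mean-square SD is √((1.34² + 2.59²)/2) = 2.062 and the difference is 2.25 − 1.00 = 1.25. The normal approximation gives 43 per group. The noncentral t with Welch degrees of freedom gives power 0.7998 at 44 and 0.809 at 45, so the smallest adequate size is 45, as stated. With 10% dropout, 45/0.9 = 50. The sample size reproduces, and 45 per arm is used below.

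**2. Two tests on the same data, no true difference.** Simulation of 40,000 trials at 45 per arm, each test at two-sided 0.05:

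| Data | t-test | Rank-sum | Either < 0.05 | Both < 0.05 |
|---|---|---|---|---|
| Normal | 5.1% | 4.8% | 6.0% | 4.0% |
| Lognormal, log-SD 0.92 | 4.1% | 4.9% | 6.9% | 2.1% |
| Lognormal, log-SD 1.0 | 4.3% | 4.9% | 7.2% | 2.1% |

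A separate run of 20,000 trials with a Welch t-test, its skewed cases set to mean 2.25 and SD 2.59, gave 6.1% (normal), 6.9% (lognormal) and 7.5% (gamma) for either test. The simulation standard error of the last figure is √(0.075 × 0.925/20,000) ≈ 0.2 points. The excess over 5% is therefore about 1 to 2.5 points per outcome.

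Across the four outcomes, treated as independent, the chance of at least one false positive is 1 − 0.95⁴ = 18.5% with one test each, 1 − 0.94⁴ = 21.9% at 6% each and 1 − 0.93⁴ = 25.2% at 7% each. The real outcomes are correlated, so these are upper values, and most of each figure comes from having four outcomes at all.

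**3. Within-group tests.** If both arms change equally and each paired test has power p, exactly one is significant with probability 2p(1 − p), and only the evolocumab arm with probability p(1 − p):

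| p | Tests disagree | Only evolocumab significant |
|---|---|---|
| 0.05 (no change in either arm) | 9.5% | 4.75% |
| 0.50 | 50% (the maximum) | 25% |
| 0.80 | 32% | 16% |

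**4. LVEF: change score against ANCOVA.** With equal variance at V1 and V6 and correlation ρ between them, the variance ratio of ANCOVA to change score is (1 − ρ²)/(2(1 − ρ)) = (1 + ρ)/2. The documents give no ρ, so it is assumed over a range. The last column is 45 divided by the ratio.

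| ρ | Ratio | Variance saved | Change-score patients per arm matching 45 under ANCOVA |
|---|---|---|---|
| 0.5 | 0.75 | 25% | 60 |
| 0.6 | 0.80 | 20% | 56.3 |
| 0.7 | 0.85 | 15% | 52.9 |
| 0.8 | 0.90 | 10% | 50 |
| 0.9 | 0.95 | 5% | 47.4 |

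**5. Hospital left out after stratified randomisation.** If hospital explains a share R² of outcome variance, the actual level of the unadjusted test is about 2(1 − Φ(1.96/√(1 − R²))). For assumed R² of 1%, 5% and 10% this is 0.049, 0.044 and 0.039. The test is conservative.

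**The case against.** The strongest reply is that the inflation rests on a rule the protocol never states. Nothing says success may be claimed on either test. If both had to be significant, the level would be about 4% for normal data and 2% for lognormal. The *and* may also be loose wording, since the primary outcome and the within-group tests use *or*, and a rule for choosing between tests is often left to the analysis plan. This stands as a limit on the size: 6% to 7.5% is conditional. It does not remove the defect, because the text fixes both tests and leaves the reading open.

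Four stronger readings are tempting, and the documents do not support them:

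- **That baseline is ignored.** LVEF and maximum CK-MB are analysed as changes, so baseline is subtracted; only the AUCs carry no baseline term. Entry requires normal CK-MB and troponin-I, so covariate adjustment would probably gain little for the enzymes.
- **That omitting hospital or using change scores raises false positives.** Omitting hospital works the other way (step 5), and change scores are valid in a randomised trial.
- **That paired tests will usually mislead.** The 50% figure is the worst case, and no section of the article bases a conclusion on them. The between-group LVEF comparison comes first. The misuse is foreseeable, not planned.
- **That 7.5% applies to each outcome.** The skewed cases in that run borrow the troponin-I mean and SD from the sample size section; the article gives no distribution for LVEF, CK-MB or the AUCs.

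It is also fair that unadjusted tests are valid and that there are only two hospitals. Adjustment is therefore a gain in efficiency, not the repair of an invalid test.

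**Conclusion.** The point holds in this limited form. Four secondary outcomes have two between-group tests and no deciding rule. If either may be claimed, each carries a false-positive rate of about 6% to 7.5% at 45 per arm instead of 5%. The within-group tests do not estimate the treatment effect and, with equal change in both arms, disagree with probability 2p(1 − p), at most 50%. The LVEF analysis gives up an estimated 25% to 5% of variance for correlations of 0.5 to 0.9, and leaving out hospital costs some precision and makes the tests slightly conservative.

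These sizes rest on an either-test reading, on assumed data shapes, on an assumed baseline-to-V6 correlation and on an assumed hospital share of variance; the documents give none of these. The primary outcome's error rate and the total of 100 patients are not affected.

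**What to change.** - **LVEF:** analyse the V6 value by ANCOVA with arm, baseline LVEF and hospital, in place of the two change-score tests.
- **Troponin-I AUC, CK-MB AUC and maximum CK-MB change:** name one deciding between-group test that accounts for hospital, for example a rank-sum test stratified by hospital, and keep the other test as a sensitivity analysis. A log-scale model is possible, but it needs positive values and turns the effect into a ratio, so it is not required here.
- **Within-group results:** label them descriptive only, with no treatment conclusion drawn from them.

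The cost is wording in the protocol and the analysis plan, settled before database lock. No extra patients, visits or measurements are needed.

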### Interim analyses {21b}

There are no interim analyses.

### Methods for additional analyses (e.g., subgroup analyses) {20b}

There are no additional analyses.

### Methods in analysis to handle protocol non-adherence and any statistical methods to handle missing data {20c}

Sensitivity analysis will be performed to handle protocol non-adherence. Both “as treated” and “per protocol” analyses will be conducted excluding any protocol violation and deviation cases. If data is lost or a patient drops out during the trial, the most recent data will be analyzed as if it were obtained at that time (last service carried forward analysis). However, during survival analysis, missing data will not be replaced, and analysis will be performed using previously collected data.

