#### Primary efficacy evaluation variable

Maximum change in troponin-I between baseline and peak level during the first 3 days after coronary artery bypass grafting

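### Carrying the last value forward is the wrong missing-data rule for a marker that rises and then falls: it understates the troponin-I peak in patients lost before the peak and distorts AUC, per-visit change and LVEF

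*Protocol article*

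**What the plan says.** Item {20c} of the protocol article fixes one rule. It applies in this case: "If data is lost or a patient drops out during the trial". Then "the most recent data will be analyzed as if it were obtained at that time (last service carried forward analysis". The article prints the word service where the usual term has observation; the description is plainly LOCF. The only carve-out is that "during survival analysis, missing data will not be replaced, and analysis will be performed using previously collected data". The rule is not limited to post-baseline values, and death is not named. The as-treated and per-protocol analyses in the same item address non-adherence, not missing values.

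The rule therefore covers:

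- **Primary endpoint:** "Maximum change in troponin-I between baseline and peak level during the first 3 days after coronary artery bypass grafting", to be "tested with an independent t-test or Wilcoxon’s rank-sum test".
- **AUC** of troponin-I and CK-MB over 3 days.
- **Per-visit change:** "Changes in troponin-I levels at each visit compared to the initial level will be analyzed with repeated ANOVA", and likewise CK-MB, BNP and CRP.
- **LVEF:** "Changes in left ventricular ejection fraction at 3 days from baseline". Table 1 schedules echocardiography only at V1 and V6.

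Three other statements bear on it. Troponin-I must be normal at entry (Eligibility criteria). The Discussion expects enzymes to rise in almost all patients within 48 h. Table 1 places the postoperative samples at 0, 6, 24, 48 and 72 h.

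**The concern.** LOCF assumes that a patient's last value stands in for later ones. Troponin after CABG starts normal, climbs to a peak and declines, so that assumption fails at nearly every time point.

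The primary endpoint is a maximum, and lower is better. A carried-forward value cannot exceed one already seen, so the rule can only understate the peak or leave it unchanged. If pre-peak losses are unequal between arms, the comparison is biased towards the arm that loses more. If they are equal, the effect is diluted.

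For LVEF, a patient without the V6 echocardiogram is recorded as unchanged, whatever the reason it is missing. In the repeated-measures analyses, filled-in values are treated as observed.

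**Working it through.** **Inputs from the documents.** Planned change 1.00 (SD 1.34) against 2.25 (SD 2.59) ng/mL; power 0.80; 45 per group, 10% dropout, 50 per group (Sample size {14}). Two-sided 0.05 (Statistical methods {20a}). Samples at 0, 6, 24, 48 and 72 h (Table 1).

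**1. The plan's own figure.** Common SD = √((1.34² + 2.59²)/2) = 2.062; difference = 1.25. The normal approximation gives 43 per group and the unequal-variance t-test 45; 45/0.9 = 50. The stated size reproduces and is not in question.

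**2. What LOCF does to one patient.** Assumed curve, as a share of peak: 0.25, 0.80, 1.00, 0.60, 0.35 at 0, 6, 24, 48, 72 h, with baseline taken as 0. AUC is taken as the area under the concentration-time curve.

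True AUC (trapezoid) = 3.15 + 16.2 + 19.2 + 11.4 = 49.95.

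| Last sample | Peak scored (true 1.00) | AUC under LOCF | Ratio to true | 72 h change scored (true 0.35) |
|---|---|---|---|---|
| Baseline only | 0 | 0 | 0 | 0 |
| 0 h | 0.25 | 0.25 × 72 = 18.0 | 0.36 | 0.25 |
| 6 h | 0.80 | 3.15 + 0.80 × 66 = 55.95 | 1.12 | 0.80 |
| 24 h | 1.00 | 19.35 + 1.00 × 48 = 67.35 | 1.35 | 1.00 |
| 48 h | 1.00 | 38.55 + 0.60 × 24 = 52.95 | 1.06 | 0.60 |

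The peak is understated only when loss precedes it. AUC and the 72 h change are too low after very early loss and too high after later loss. The crossover depends on the curve: with 0.3, 0.7, 1.0, 0.6, 0.4, loss after 6 h gives an AUC of 49.2 against a true 49.5.

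**3. LVEF.** With measurements at V1 and V6 only, LOCF gives V1 − V1 = 0 for every missing V6.

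**4. Effect on the primary comparison.** Assumptions: lognormal data, no true effect (both arms mean 2.25, SD 2.59), 50 per arm, and k patients with only a baseline sample, scored 0. The false difference is (k_test − k_control)/50 × 2.25.

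| Scored 0, test vs control | False difference (ng/mL) | Two-sided rejection, t-test | Rank-sum |
|---|---|---|---|
| 1 vs 0 | 0.045 | 4.7% | 5.2% |
| 3 vs 0 | 0.135 | 5.2% | 6.8% |
| 5 vs 0 | 0.225 | 6.9% | 11.8% |
| 3 vs 2 | 0.045 | 4.0% | 3.6% |
| 5 vs 5 | 0 | 3.2% | 2.0% |

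These come from 20,000 simulated trials per row; repeat runs agree to within about one percentage point. The worst-case 0.225 is 0.225/1.25 = 18% of the planned effect. If the five patients are instead left out at random, rejection is 4.5% and 5.0% (4,000 trials). If the five losses are all among controls, rejection is similar (6.1% and 10.9%) but almost always against evolocumab.

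**5. Balanced loss under the planned effect.** With 5 of 50 per arm scored 0: 0.9 × 2.25 − 0.9 × 1.00 = 1.125, a 10% dilution.

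**The case against.** The best defence is that few patients will be affected. The primary window is the first 72 h after surgery, when patients are in hospital: Table 1 puts discharge at 7 ± 3 days, and the Trial design section plans daily blood tests including cardiac markers. The drug is a single preoperative dose. The 10% dropout is an allowance for the whole one-month study, and loss after discharge cannot touch the peak. All of this stands. It limits the likely size but does not make the rule suitable.

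A reader might infer more than the article supports:

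- **That early losses always get the best possible score.** This holds in practice only for the primary peak, and only with no postoperative sample. Later loss often makes AUC and per-visit change look worse, and an LVEF change of 0 is neutral.
- **That deaths are deliberately scored as low injury.** Item {20c} speaks of lost data and dropout and does not name death. It reaches early deaths only because no other rule is given for the biomarkers. Mortality itself is analysed without replacement.
- **That the trial is biased towards evolocumab.** This requires more pre-peak losses in the test arm. Open-label conduct makes unequal loss possible but does not show it.
- **That standard errors for the primary test are too small.** This was not shown; with balanced loss the tests are conservative.

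**Conclusion.** The concern holds in a limited form, as a should-fix. LOCF is a stated rule covering every analysis except survival analysis, so this is not detail left to an unseen analysis plan. For the primary endpoint it understates the peak in anyone lost before it and is harmless afterwards. For AUC and per-visit change the direction depends on when the patient is lost, and for LVEF it manufactures zeros.

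The effect on the primary test is probably small: error stays near 5% with one unbalanced loss and is about 5% (t-test) and 7% (rank-sum) with three. It reaches about 7% and 12% only if all five allowed losses fall in one arm, none in the other, and none has a postoperative sample. Equal losses instead shrink the planned difference to 1.125 ng/mL. These sizes rest on the lognormal shape and assumed loss patterns; the article gives no expected number lost before the peak.

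**What to change.** Amend item {20c} and carry the change into the analysis plan:

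- **Main rule:** remove LOCF. It may stay only as a labelled sensitivity analysis.
- **Peak and AUC:** do not carry baseline or pre-peak values forward. Multiply impute missing V2–V6 values on the log scale from arm, baseline and observed visits, then derive peak and AUC.
- **Deaths before 72 h:** name them explicitly and add a rank-based sensitivity analysis giving them the worst rank.
- **Per-visit troponin-I, CK-MB, BNP and CRP:** use a likelihood-based repeated-measures model on observed values, with nothing filled in.
- **LVEF:** do not set missing changes to 0. Use multiple imputation, or observed cases with a sensitivity analysis.

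The cost is revised wording and modest extra programming. No new data are needed and the sample size does not change.
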